### Plans to promote participant retention and complete follow-up {18b}

Participants who discontinue the intervention will be offered the choice not to receive any additional weekly ratings, but will be asked to respond to post-treatment and at follow-up assessments. Hence, outcome data will be collected from the entire ITT sample at post-treatment and all follow-up points. Participants are allocated self-rating forms over the Internet and receive an email notification regarding this. Two and 4 days following the allocation, they receive automatic text message (SMS) reminders if they have not completed the forms. After this, participants that still have not completed their forms are contacted per SMS and phone by the study coordinators. No financial or material rewards are given to the participants for filling out the forms. However, at the follow-up assessment after 12 months, participants are informed that 100 SEK are given to charity organizations for each participant completing the follow-up measurements.

### Data management {19}

The study’s data management will follow the established procedures for studies on Internet-based treatments [48]. These procedures have been applied in a vast number of studies conducted over several years. All individuals who participate in the project will be assigned a unique ID that will be used throughout the project to communicate via the Internet. All correspondence with the participants will be made through a secure communication system; importantly, no communication with participants will occur via standard email. All communication and data collected through Internet-based self-report measures will be exclusively associated with each participant’s unique ID, and no personal information shall be discussed. During the project, all data (i.e. communication and data from self-report measures) will be stored in an encrypted database. Access to this database is controlled by the computer system so that the PI and the study coordinators have complete access to view. No one can change the values in the database and everything is logged. Personal information will be stored in a fireproof safe that solely the study administrators can reach. The key that links participants to their unique IDs will be stored in a separate fireproof safe to fulfil the regulations concerning safe data storage, and the data management procedures adhere to GDPR.

### Confidentiality {27}

All data are kept confidential through automatically generated study codes that are given to each participant. Data about a certain participant on the Internet platform and in the data base will solely use this study code as the identification. The identification key that connects the participant’s study code to the actual personal information (full name, Swedish personal identification number, and address) is stored in a fireproof safe that solely the study administrators can reach.

### Plans for collection, laboratory evaluation and storage of biological specimens for genetic or molecular analysis in this trial/future use {33}

Not applicable. No biological specimens will be collected.

## Statistical methods

### Statistical methods for primary and secondary outcomes {20a}

Statistical reporting will follow the CONSORT standards [49]. All participants who are randomly assigned to a condition shall be entered into the main analysis (intent-to-treat analysis = ITT) of the primary outcome measure (QIDS-A17-SR) at the primary assessment point of treatment termination (10 weeks). A secondary analysis of the primary outcome measure will include a per-protocol analysis.

In order to fully explore trajectories of change, a multilevel growth curve level strategy [50] will be employed for measures assessed weekly, comparing estimated change in depressive symptom severity from baseline to end of treatment between groups. Differences in efficacy between conditions will be investigated by modelling interaction effects of group and time. These methods have been recommended for RCTs that investigate Internet interventions [51]. One important advantage is their ability to handle missing data using a maximum likelihood estimation [52]. Non-inferiority will be defined as fulfilled when the upper 90% confidence interval of the estimated QIDS-A17-SR for the IPDT group at treatment termination is below the estimate for the ICBT group plus *d* = 0.30 (i.e. the non-inferiority margin).

The number of patients who changed reliably, as estimated by the Reliable Change Index (RCI [53]), will be reported to provide an estimate of improvement/deterioration in each group that is not attributable to chance. Response will be defined as reliable improvement (i.e. improved more than the RCI), whilst also scoring at least 2 SD below the pretreatment mean. Partial response will be defined as fulfilling the RCI whilst scoring less than 2 SD below the pretreatment mean. Remission will be defined as scoring 6 or below on the QIDS-A17-SR [33].

Secondary outcomes will be analysed primarily according to ITT and with treatment termination as primary assessment point. Mean scores at termination will be compared across groups using analysis of covariance (ANCOVA) controlling for baseline scores.

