**Methods:**

The study will employ a parallel randomized non-inferiority design (ratio 1:1; *n* = 270). Eligible participants are adolescents 15–19 years suffering from depression. The primary hypothesis is that IPDT will be non-inferior to ICBT in reducing depressive symptoms from pre-treatment to end of treatment. Secondary research questions include comparing outcomes of IPDT and ICBT regarding anxiety symptoms, emotion regulation and self-compassion. Additional data will be collected to evaluate cost-effectiveness as well as investigating predictors, moderators and mediators of outcome. In addition, we will examine long-term outcome up to 1 year after end of treatment. Diagnostic interviews with MINI 7.0 will be used to establish primary diagnosis of depression as well as ruling out any exclusion criteria. Both treatments consist of eight modules over 10 weeks, complemented with therapist support through text messages and weekly chat sessions. Primary outcome measure is the Quick Inventory of Depressive Symptomatology in Adolescents Self-Rated (QIDS-A17-SR). Primary outcome will be analysed using data from all participants entering the study using a multilevel growth curve strategy based on the weekly measurements of QIDS-A17-SR. The non-inferiority margin is defined as *d* = 0.30.

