### Sample size {14}

In order to assess non-inferiority and superiority using a repeated-measures design, power calculations for two-level LMMs were made following Galbraith and Marschner [29] using the R-package powerlmm v. 0.4. A non-inferiority bound of *d* = 0.30 was set alongside an α at 0.05, a variance ratio of 0.75, an attrition rate of 20% and intermittent missing data on weekly measures of 20%. Based on these calculations, a total sample size of 270 is needed to reach 80% power. The power analysis is based on data from the pilot trial [23]. The non-inferiority margin was based on earlier non-inferiority studies comparing face-to-face PDT to CBT in adults suffering from depression, in which Cohen’s *d* = 0.30 was considered as a minimal clinically meaningful difference. Driessen et al. [30] defined non-inferiority as Cohen’s *d* = 0.30 for all continuous outcome measures. Connolly Gibbons et al. [31] defined non-inferiority as 2.5 points on the Hamilton Depression Rating Scale, which was equivalent to a Cohen’s *d* of 0.29.

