## Assignment of interventions: allocation

### Sequence generation {16a}

Eligible participants will be randomized to one of the two arms (1:1 ratio). An independent researcher who is not involved in the study will conduct the randomization procedure via a computerized random number service (random.org). Randomization will be done in blocks of various sizes pending on the amount of adololescents found eligible at each inclusion conference during the project reqruitment period.

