## Data collection and management

### Outcomes {12}

The primary outcome will be severity of depressive symptoms, defined as the difference between groups in estimated change in depressive severity from baseline to end of treatment (10 weeks). Secondary outcomes will be anxiety symptoms, emotion regulation and self-compassion at treatment termination. In addition, long-term outcome in depressive and anxiety symtoms is measured at follow-up up to 1 year after termination. See the section “Data collection and management” below for details about the instruments used for measuring these outcomes.

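### The non-inferiority rule puts a confidence limit on the IPDT arm only and treats the ICBT estimate as known; applied as written, its type I error is about 12%, not 5%.

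*Protocol article*

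**What the plan says.** The article gives one criterion for non-inferiority, in Statistical methods for primary and secondary outcomes {20a}. It requires that "the upper 90% confidence interval of the estimated QIDS-A17-SR for the IPDT group at treatment termination is below the estimate for the ICBT group", with d = 0.30 added to the ICBT estimate.

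Three other statements bear on that sentence:

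- Outcomes {12} defines the primary outcome as "the difference between groups in estimated change in depressive severity from baseline to end of treatment (10 weeks").
- Sample size {14} fixes the error rate: "A non-inferiority bound of *d* = 0.30 was set alongside an α at 0.05". It also says that "a total sample size of 270 is needed to reach 80% power".
- Earlier in the same paragraph of {20a}, efficacy differences are to be examined through the interaction of group and time in a growth model.

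Nowhere does the article say that the 90% interval is the interval of the between-group difference.

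**The concern.** The rule compares an upper confidence limit for one arm's estimated score with the other arm's point estimate shifted by a constant. The ICBT mean is estimated from about the same number of participants as the IPDT mean, yet the rule treats it as a fixed number. The variance on the decision scale is therefore too small, and the limit lies too close to the observed difference.

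The quantity is also not the declared one. The rule uses a level at termination in one arm, whereas the primary outcome is a difference between arms in change.

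Non-inferiority is the trial's primary question, and this sentence decides it. The error favours a claim of non-inferiority. Under Who will be blinded {17a}, masked analysts run the test in both directions and one result is kept. They need a rule that can be carried out as written. One analyst following {20a} to the letter and another following {12} could reach opposite conclusions from the same data.

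**Working it through.** **Inputs from the article:** margin d = 0.30; alpha 0.05; total 270 with 1:1 allocation, so 135 per arm; 80% power; a 90% interval, so the multiplier is 1.645 if two-sided.

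**Assumptions, not in the article:** equal standard errors and independent arm estimates. Both are varied in step 4.

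**1. The plan's own figure.** For two means with a one-sided 5% test of the difference, n per arm = 2(1.645 + 0.842)²/0.30², which rounds up to 138, or 276 in total. With 135 per arm the power is 79.4%. This ignores the planned 20% attrition; 276/0.8 = 345. The article used a two-level mixed model, whose result cannot be reproduced exactly because the intraclass correlation and the time scaling are not given. An analytic version with variance ratio 0.75, 20% dropout, 20% intermittent missing data and time scaled 0 to 1 gives:

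| Assumed intraclass correlation | Power, one-sided 5% |
|---|---|
| 0.4 | 70–71% |
| 0.5 | 77–78% |
| 0.6 | 84–85% |

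So 270 for 80% power is attainable at a correlation of roughly 0.5 to 0.55, with a one-sided 5% test of a between-arm contrast. That makes 5% one-sided the natural benchmark for the decision rule.

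**2. Error of the written rule.** Let m_I and m_C be the arm estimates with standard errors SE_I and SE_C. The rule passes if

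m_I + 1.645·SE_I < m_C + margin.

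When the true difference equals the margin, m_I − m_C − margin has mean 0 and standard error √(SE_I² + SE_C²). Hence

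type I error = Phi(−1.645·SE_I/√(SE_I² + SE_C²)).

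With equal standard errors this is Phi(−1.645/√2) = Phi(−1.163) = 12.2%. Against 5% that is a factor of 12.2/5 = 2.4.

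**3. Simulation.** With 135 per arm, a true difference at the margin and 40,000 trials, the written rule passed in 12.2% and the interval for the difference in 4.9%.

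**4. Sensitivity.**

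| Assumption | Type I error of the written rule |
|---|---|
| SE_C/SE_I = 0.8 | 9.9% |
| SE_C/SE_I = 1.25 | 15.2% |
| Equal SEs, correlation of arm estimates 0.1 | 11.0% |
| Equal SEs, correlation 0.2 | 9.7% |
| Equal SEs, correlation 0.3 | 8.2% |
| Equal SEs, correlation 0.5 | 5.0% |

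A positive correlation could arise if the model gives both arms a common baseline. It would have to reach 0.5 before the written rule held 5%. If the 90% limit is read as a one-sided bound, the error is Phi(−1.282/√2) = 18.2%.

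**5. What it means on the effect scale.** With SD 1 and complete data, SE per arm = 1/√135 = 0.086 and SE of the difference = √2 × 0.086 = 0.122. The written rule passes for observed differences below 0.30 − 1.645 × 0.086 = 0.16. The correct rule passes below 0.30 − 1.645 × 0.122 = 0.10. Observed differences between 0.10 and 0.16 SD in favour of ICBT would change the conclusion.

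**6. Power.** In a design with 80% power for the correct rule, margin/SE of the difference = 0.842 + 1.645 = 2.487. The written rule then passes with probability Phi(2.487 − 1.163) = 90.7% at a true difference of zero, so it does not match the stated power either.

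**The case against.** The strongest reply is that the sentence is loose shorthand. An upper limit for IPDT below ICBT plus the margin can be heard as an upper limit for IPDT minus ICBT below the margin, with ICBT as the reference arm. The context supports that reading. The primary outcome is a group difference, the model term is a group-by-time interaction whose standard error includes both arms, the margin is a between-group effect size, and 270 fits a one-sided 5% test of a contrast. If the analysts work that way, alpha stays at 5%. A separate analysis plan may already say so.

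This stands in part. The 12% describes the rule as written and does not prove that the analysis will run at that rate. The figure also depends on the assumptions above; at a correlation of 0.3 the error is 8.2%, which is less than double the planned rate. The 18.2% figure needs a second, less likely reading, because a two-sided 90% interval is the one that matches alpha 0.05.

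The reply does not rescue the sentence. To say that a contrast was meant is to say that the written criterion is wrong. The article does not leave the point to another document: it states an explicit rule that disagrees with its own outcome definition and alpha.

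**Conclusion.** The concern holds. The criterion in {20a} omits the sampling error of the ICBT estimate and is inconsistent with {12}, with the model described in {20a} and with the alpha in {14}. Carried out as written, with equal standard errors and independent arm estimates, it has a type I error of 12.2% at the margin. The range is 8.2% to 15.2% for standard-error ratios of 0.8 to 1.25 (independent arms) and correlations of 0 to 0.3 (equal standard errors). If an interval for the difference was always intended, this is a wording error with no effect on alpha. It must be corrected in either case because it governs the primary conclusion. The sample size is not in question here.

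**What to change.** Replace the sentence in {20a} with a rule on the contrast: non-inferiority is shown if the upper limit of the two-sided 90% confidence interval for the model-estimated IPDT minus ICBT difference in QIDS-A17-SR change over the 10 treatment weeks lies below the margin, with both expressed on the same scale. State that this is a one-sided test at 5%, and apply the same form to the mirror-image test run under masking.

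The cost is one sentence in the protocol or analysis plan, dated before the arms are unmasked. No new data and no change to the model or to the 270 participants are needed. The interval is wider by a factor of √2 under the equal-variance, independent-arms assumption, but it is the one that matches the stated alpha and power.

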### Interim analyses {21b}

No interim analyses will be conducted. However, analyses of attrition will be conducted in order to increase the sample size in case of unexpectedly high attrition from weekly or post-treatment assessments.

### Methods for additional analyses (e.g. subgroup analyses) {20b}

No subgroup analyses are planned for the main outcome paper. Instead, moderator analyses will be conducted at a later stage (subsequent to the main outcome paper) to analyse whether certain factors predict differential suitability to the interventions.

### Methods in analysis to handle protocol non-adherence and any statistical methods to handle missing data {20c}

All primary analyses will be conducted according to ITT, using linear mixed modelling (LMM). LMM handles missing data with maximum likelihood estimation. Secondary analyses of the primary outcome measure will include a per-protocol analysis (PPA, which includes all participants who adhered to the protocol). Per protocol analyses will include completers, defined as the combination of having completed at least five modules (defined as completing at least one exercise per module), having attending at least five chat sessions and completing the post-treatment assessment.

## Oversight and monitoring

### Composition of the coordinating centre and trial steering committee {5d}

The Trial Steering Committee (TSC) will be composed of all investigators (authors). The TSC will meet according to key milestones and will have responsibility for project oversight, meeting key milestones, methodological and statistical conduct of the research, reporting to funder, review of risks and issues and ensuring the scientific integrity of the protocol and conduct of the study.

### Composition of the data monitoring committee, its role and reporting structure {21a}

The Data Monitoring Committee is composed of an independent researcher, an administrator and a clinician not otherwise involved in the study. The primary aim of the DMC will be to monitor progress of the study (e.g. reviewing recruitment and retention rates) and to review participant safety; all serious adverse events (SAEs) will be reported to and reviewed by the DMC as will any participant experiencing substantial psychiatric problems at treatment termination. The DMC will also make periodic checks of data completeness and accuracy.

### Adverse event reporting and harms {22}

All SAEs (e.g. suicide risk, substance misuse, ongoing maltreatment, or sexual abuse) during treatment will be registered by the principal investigator and the DMC. In addition, as suggested by Rozental et al [54], any negative effects will be monitored and reported. At post-assessment in a questionnaire with open questions, the participants will be urged to express their thoughts and feelings about their respective treatments and therapists as well as describe any adverse experiences whilst under treatment.

### Frequency and plans for auditing trial conduct {23}

Stockholm University does not have a specific unit for auditing trial conduct. The research group contains members both with allegiance to PDT and CBT, respectively, to ensure that both treatments are conducted in an adequate way. An independent researcher, external to the study’s project group, will be present and monitor the procedures as the database is extracted from the Internet platform and masked with regard to treatment arm prior to the outcome analysis.

### Plans for communicating important protocol amendments to relevant parties (e.g. trial participants, ethical committees) {25}

It is highly unlikely that important protocol modifications will occur. If we should consider any such modification, we will first have to apply to the Swedish Ethical Review Authority for permission to undertake these modifications. If modifications are undertaken, they will be reported to the trial registry ISRCTN. Changes to the protocol will also be reported in publications of the study’s findings.

### Dissemination plans {31a}

The primary outcome paper will be open-access and present outcome data in a peer-reviewed journal. No outcome data will be published or presented before the data collection process is completed. Subsequently, the results will also be presented at scientific conferences and in popular science texts that are comprehensible for a wider public. A popular science summary of the results will be posted online for laymen and study participants.

## Discussion

The need to develop early, brief, focused and effective interventions for depressed adolescents is urgent. Internet-based interventions are designed to reach, amongst others, people who do not access youth mental health services, or seek or receive traditional psychotherapy. One aim is to increase their access to psychological treatments, as well as increase such treatments’ cost effectiveness. Making treatment more easily accessible might also propose major health benefits because accessible treatment enables adolescents to apply for and receive treatment at an earlier stage of a psychiatric disorder. Internet-based interventions also have the potential to reach patients who would otherwise avoid seeking treatment due to social stigma [55]. It has been suggested that Internet-delivered treatment might also be useful for reaching adolescents with more severe symptoms who are reluctant to seek care on their own [56].

Empirical support has already been established for ICBT and the ICBT protocol used in the present study achieved clinical significant change in 46% of cases [10]. Preliminary results from the pilot IPDT trial suggest similar response rates. The trial is based on an extensive power analysis, based on data from two previous trials as well as a pilot trial, and especially taking the specific statistical analyses that are planned (i.e. multilevel modelling) into account. This trial is designed to investigate whether or not IPDT is non-inferior to ICBT with regard to depressive symptoms as well as determine whether or not the treatments are comparable regarding cost-effectiveness, thereby increasing treatment alternatives. Several secondary outcome measures are also assessed, in order to investigate possible differential effects of the treatments. Furthermore, we hope that the future moderator analyses will provide information regarding which adolescents will benefit the most from ICBT and IPDT, whilst mediator analyses will shed light on possible different treatment trajectories and processes.

This study compares two active treatments based on the hypothesis that they do not differ in effect. Conditions are matched in time, frequency and amount of contact, thereby reducing possible effects of such structural factors. One limitation is that we do not have an inactive control group to adjust for possible spontaneous remissions or regression to the mean, although both treatments have been previously tested against inactive control conditions with large effects. Furthermore, inactive control conditions for depressed children are ethically difficult to justify, which is why we wanted to avoid their inclusion in the present trial. In addition, waiting lists are not recommended as comparison groups [57].

The inclusion of measures of several potential moderators and mediators allows for an investigation of various pathways of change in the two treatments as well as an exploration of the possible factors that influence “what works for whom”. Increasing treatment alternatives is of utmost importance as response rates suggest that a substantial proportion of patients do not respond to existing, evidence-based treatments. In the future, if IPDT would prove non-inferior compared to ICBT, it would be relevant to conduct a cross-over-study, investigating whether patients not helped by one of the treatments would be helped by the other. The use of a guidance protocol ensures that conditions are matched in terms of guidance and amount of contact. Adverse events shall be rigorously tracked, and participants will be asked about any negative effects that result from their treatments.

This trial is the first to compare the effects of IPDT on adolescent depression to those of another active treatment. This trial’s results will be significant for expanding the range of time- and cost-efficient treatment alternatives to adolescents who suffer from depression, a group who immensely needs such attention.

